## 5. TREATMENT OF SUBJECTS

All home office workers who will participate in the study will be asked to continue their work as they are used to do. During the workday all participants are exposed to the illumination of the existing general indoor lighting in their home. Depending on their desk location, participants may be exposed to daylight entering the office space through windows. This additional light will not contain UVB irradiance as UVB irradiance is absorbed by the window glass.

In addition to the standard lighting the **intervention group** will receive an additional personal desk-based luminaire that is positioned at the side of participant's home desk. The participants in the intervention group will be asked to be seated closer to one side of the desk, where the free floor standing luminaire is positioned, in order to sit more effectively under the luminaire. The area to be seated will be marked on the desk with stickers and tape. Figure 4 demonstrates the desk-based intervention lighting device placed at the side of the desk. Care is taken that the distance between the participant receiving a luminaire and the neighbor (non-participating) colleague/family member is more than 1.6 m to prevent that the (non-participating) colleague/family member is exposed to the ultra-low doses of UVB. The designated workspace of the control group is not altered for the purpose of the study. Control participants will experience only the existing general lighting in their home office).

The desk-based luminaire will emit a continuous ultra-low and safe daily artificial UVB irradiance (actinic UV) of less than 6 mW/m^2 at 20 cm resulting in a received dose by the office worker sitting at his/her desk of about 0.45 SED ((UVI = 0.06) during office hours. The lamps are turned on automatically at 8.50 and off at 17.10 hr. A longer (over)-exposure is therefore not possible. Both groups can do their daily work as they are used to do. Both the participants and the people living in their home will be advised to respect the indicated minimum application distance (80 cm). This minimum application distance keeps the Actinic UV exposure within Risk Group Exempt limits, which allows for a continuous exposure of 30000 sec per day (8 hrs. and 20 minutes) according to the IEC62471 (see form *D6\_2 Photobiological safety IEC 62471 ed 1.0*).

[figure not shown]

**Figure 4.** A picture of a currently designated workspace equipped with the desk-based lighting device.

## 6. INVESTIGATIONAL PRODUCT

### 6.1 Technical description

In order to investigate the effectivity of adding **ultra-low** dose(<0.5 SED, UVI ≈0.06), but safe (according to the IEC62471) UVB irradiance in a general office lighting solution, a special lighting research device is developed according to the general lighting guidelines with respect to photobiological safety, mechanical and electrical requirements. The newly developed luminaire is based on a released, commercially available Free Floor Standing product (<https://www.lighting.philips.com/main/prof/indoor-luminaires/free-standing/smartbalance-free-floor-standing> and D6\_5 CE declaration of commercial available smart\_balance). The standard product is modified in such a way that

- Uplight is removed
- Downlight is reduced
- UVB light is added
- Light exit window is replaced by a UVB resistant version
- Drivers are replaced in line with new led configuration
- Bluetooth control is added to set the on-off rhythm and level.
- The level can only be configured by trained people and within safe limits.

The special lighting device is designed for research purposes towards new opportunities for general lighting and will not be commercialized as is.

The newly-developed luminaire-prototype emits visible and a very low amount of invisible (UVB) irradiation exposing unprotected skin and eye, and enabling natural processes that occur when the body is exposed to daylight; Therefore special attention has been dedicated to the photobiological safety as this is seen as the major modification of the free floor standing luminaire:

- Direct view to the naked UVB LED is prevented by the diffuser and in the event the diffuser is removed from the head, the UVB LEDs go off.
- Over exposure is prevented by limitation of the maximum UVB output by a firmware setting in the driver and a real time clock automatically turns on and off the light output (30.000 s).
- The personal desk-based lighting intervention will be checked on UVB irradiance levels on a regular basis to ensure a consistent dose during the pilot study. The relative stability will be monitored by a point measurement via solar meter model 6.5 (UV) at 20 cm of the head of the luminaire. Additionally, a continuous daily dose measurement is conducted by placing wear shade dosimeters at the desk.
- Device labeling and instruction to the user to not stare in the luminaire head and to prevent prolonged exposure to distances shorter than 80 cm.

Since the UV irradiance is the innovative part in this device, [name], Atmospheric Radiation from Manchester University has run an independent test (see *D6\_1 Analysis of Signify Luminaires\_FINAL*) to confirm the radiance measurements made by the lighting quality center in Eindhoven, to ensure safety to the users. The main conclusion from this report is that “the luminaires meet all safety requirements for intended use if the affixed safety label states a safe distance of 800 mm. People who do not wish to receive radiation from the luminaires should be seated > 1.6 m from the point beneath the center of the LED housing, as this is the distance at which the irradiance is reduced to 10% of the central maximum and can be considered negligible from the perspective of biological effects.”

For more information and details on the desk-based lighting device we refer to the investigator's brochure and associated documents (*D1 investigator's brochure and risk analysis\_v2*, *D6\_2 Photobiological safety IEC 62471 ed 1.*; *D6\_3 Example of biological safety evaluation report HJ11814*);

The personal desk-based lighting device carries a CE mark with document no FS484F UV-B DoC (*D6\_8 CE Declaration of Conformity (FS484F UVB DoC)*)

[figure not shown]

**Figure 5.** Illustrated (safe) use of the luminaire and the caution labels

## 6.2 Operating behavior

### *First day luminaire behavior*

After the first blood sampling has been taken place, the luminaire will be powered by putting the plug in the mains socket by the technical team. When the luminaire is connected to power it will start with dimmed white light and no UVB. A small amount of white light is emitted to indicate that the luminaire is ON. At noon or when powered after 13.00 hr, the next morning, the luminaire will switch ON (full brightness and UVB) according the preset schedule: ON at 8.50 hr and OFF at 17.10 hr (both the white and UV-B light will turn off). This behavior will also occur in case of a power cycle / disturbance in power.

*Luminaire behavior during the study*

The luminaire will automatically switch ON (full brightness and UVB) at 8.50 hr according to the preset schedule. At 17.10 hr both the white and UV-B light will turn off. This will be repeated for all days during the study period as long as the luminaire is powered. The simultaneous switching on of the visual white light and the UVB lights is an additional visual cue to the participant and other people living in the home to remind them that there is UVB irradiance and that directly looking into the luminaire should be avoided.

The luminaire is equipped with caution labels and a user manual will be supplied to the participant to facilitate proper use of the luminaire and easy access to a contact person if questions pop up.

## 7. METHODS

### 7.1 Study parameters/endpoints

#### 7.1.1 *Main study parameter/endpoint*

For the primary objective, the serum 25(OH)D will be investigated. The blood sampling (one tube of 4 ml blood per measurement) will be conducted by a medically trained person of DVU as a formally recognized health provider. The actual serum 25(OH)D analyses will also be conducted by DVU. This measure will be collected at baseline, after 4 weeks of the intervention, and after 8 weeks of the intervention.

#### 7.1.2 *Secondary study parameters/endpoints (if applicable)*

Secondary parameters include self-report measures:

- A validated survey on general fatigue will be filled in at each measurement point, the Checklist Individual Strength [43]. In addition, several items on sleep timing and quality, averaged over the past two weeks (as in the Checklist Individual Strength) will be completed in the survey. The questions on sleep timing and quality are based on the Consensus Sleep Diary and the Munich Chronotype Questionnaire (but asked as averaged over the past two (instead of four) weeks; see [44] and [45]). In addition, vitamin D related food intake during the past four weeks will be collected (based on [46]). The questions will be programmed in the LimeSurvey tool used at the Technical University of Eindhoven. Responses on these questions will only be saved locally on the encrypted TU/e server.
- Desk presence data, time spent outside, and exposed body surface area: These data come from self-assessment which will be facilitated on hard-copy pre-defined tables during the luminaire placement. In this diary, participants will report on the amount of time (hours and minutes) spent at the desk in the morning hours (8:50-13:00) and afternoon hours (13:00-17:10). In addition, they report the time spent outside (hours and minutes) in daylight between 8:50 and 17:10. They will also report this on Monday for the previous weekend days. Finally, they report on the body parts that are not covered by clothing (e.g. neck, face, under arms, upper arms, hands etc.). Participants will be asked to upload a scan/photo of the daily diaries every week on Friday in the same LimeSurvey tool as is used for the other questionnaires.

#### 7.1.3 *Other study parameters (if applicable)*

- Age, gender, and amount of working hours each day will be assessed at the start of the baseline week in order to enable description of both groups. Questionnaires will

also be programmed in LimeSurvey and sent via a link to participants. Subsequently, participants can fill in the questionnaires on their own (work) laptop.

## 7.2 Randomisation, blinding and treatment allocation

For a full visual overview of the allocation procedure see Figure 6. The independent agency CG selections will make a selection of eligible participants based in the in- and exclusion criteria (see sections 4.2 and 4.3). A list with eligible participants who are interested in participating in the study is mailed to the responsible researcher at the TU/e who will perform block randomization for assignment to the conditions. However, in case insufficient participants are available who work at least 2.5 days at their home office, selection for the intervention group will then be based on presence at the desk (at least 50%). This selection is believed not to influence the primary outcome parameter (25(OH)D serum levels) and as such the conclusions around the primary objective: Participants will not receive any (noteworthy, see [39]) UVB exposure (that could influence the serum 25(OH)D) unless they are allocated to the intervention group. In the statistical analysis, care will be taken to control for potential group differences in desk presence, time spent outside and vitamin D intake by food.

[figure not shown]

**Figure 6.** Allocation procedure

In addition to randomization, blinding is frequently applied to prevent that participants know they are in the control or intervention group. For this specific pilot, only 14 luminaires are available. These luminaires will be placed at the side of the participant's desk when allocated to the experimental group. As such the participant is aware that he or she will receive UVB. Blinding by reducing the sample size to 14 instead of 28 has been considered. However, to prevent that the data can be allocated (identified) to individual persons and to have sufficient power in the study, the total number of participants is estimated to be >25 in total. Since the 25(OH)D levels will not be affected by a pseudo-randomization and non-blinding strategy, it has been chosen to secure privacy of the participants and prioritize a sufficient sample size, and blinding is compromised.

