### 3. STUDY DESIGN

A pilot study with a between-subjects manipulation is proposed for the current study design. The type of light (artificial UVB supplementation vs. no artificial UVB supplementation) is manipulated between subjects. In both the intervention group and the control group, repeated measures are employed during a sampling period of 8 weeks. When possible, randomization over the two groups will be conducted (see section 5.2 for more information). Figure 1 gives a graphical representation of the study design.

[figure not shown]

**Figure 1.** Graphical representation of the study design

For the primary objective, the serum 25(OH)D will be investigated. At the start of the study (day 0), participants will be asked to donate 4 ml blood to determine the baseline 25(OH)D levels in their blood. Subsequently, the light intervention is installed at the desks in the home office of participants in the intervention group delivering the ultra-low dose of UVB during daytime. The control group will not be exposed to artificial UVB radiation and will not receive a lamp at their desk.

The blood sampling and serum 25(OH)D analyses will be repeated in Week 4 and Week 8 on pre-scheduled morning time slots, preferably the same day for all participants, and is conducted by Diagnostiek Voor U (DVU) as a formally recognized health-care provider.

The self-reports on food intake (only vitamin D related), subjective sleep timing and quality, and general levels of fatigue will be investigated through (validated) questionnaires. Both the control and intervention group will receive the questionnaires electronically (via LimeSurvey) in the mornings during which blood sampling is also conducted. The second and third questionnaire contains an option for the participant

to give any comments or feedback about the study (procedure and intervention) to gain some additional insight in their study experience. Table 1 gives an overview of the frequency and timing of the data assessments. These assessments are all conducted in both groups.

**Table 1** Overview of the frequency and timing of the different questionnaires and serum 25(OH)D level measurements

|                                                      | Day 0 | Day 29-31 | Day 58-60 |
|------------------------------------------------------|-------|-----------|-----------|
| General information                                  | X     |           |           |

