### 4.3 Exclusion criteria

The exclusion criteria include:

- Current pregnancy, breast feeding or a desire to become pregnant
- Having children at home aged 10 years or younger
- Having malignant skin conditions in the past or currently
- Photosensitive medical conditions or photo-sensitising drugs
- Users of medicines and/or cremes mentioning in the prescription as side effect extra sensitivity to the sun / interaction with sun exposure
- Planned use of sun beds, or sunbed use during the past 4 weeks
- Currently taking or planning to take oral vitamin D3 supplements or have been taking D3 supplements during the past 4 weeks.
- High vitamin D levels at the start of the study (>375 nmol/L) which need medical attention [41]

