**7.3.3*****Main study parameter: Vitamin D3 serum levels***

The blood sampling procedure and serum analysis will be conducted by Diagnostiek Voor U Eindhoven (DVU) as a formally recognized health provider. DVU will send the blood sample results combined with the initially assigned Participant ID's via an encrypted e-mail to the HTI researcher who will double code (pseudonymize) this data before sending it to the data-analyst ([name]). Participants give consent for DVU sharing this data with the TU/e researcher via the consent form. No diagnosis or advice can and will be given based on the serum vitamin D3 levels. If participants have any questions regarding the gathered blood values, they can turn to their general practitioner or contact DVU. Serum 25(OH)D values will be stored for long-term at the local secured TU/e server (15 years). DVU U will destroy the actual blood samples 5 days after the blood analyses have been conducted at the laboratory. DVU will store the coded vitamin D blood values for a period of 20 years.

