### 7.4.1.2. Questionnaires

Questionnaires to be found in F1 Questionnaires v2.0 20200515 will be programmed in Limesurvey (a locally installed tool used at the TU/e where only local storage of the data is enabled). The questionnaires are sent via a link to the participants' e-mail on the day of the blood sampling (in the morning). Subsequently, participants can fill in the questionnaires on their own PC/laptop. General levels of fatigue will be measured through the 20 items of the Checklist Individual Strength [43], sleep quality and timing are assessed through 19 items based on the Consensus sleep diary [44] and the Munich Chronotype Questionnaire [45]. The first online questionnaire (sent at day 1 in week 0) also includes questions related to the target group description like age, gender, and vitamin D related food intake (see section 5.1.3; food intake will also be measured in week 4 and 8). Participants will receive a reminder to complete the questionnaire towards the end of the working day if they have not completed the questionnaire yet. They can also do this at home since no IP addresses are saved by the Limesurvey tool.

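### Section 7.2 says non-blinding cannot affect 25(OH)D, but supplement and sunbed use, which can raise it and may differ by arm, are screened at entry and not described as recorded in the 8 weeks

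*Protocol*

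**What the plan says.** **Blinding.** Section 7.2 explains that only 14 luminaires exist and that a participant with a lamp knows it. It then accepts the open design: "Since the 25(OH)D levels will not be affected by a pseudo-randomization and non-blinding strategy". The only supporting reason in that section is offered a little earlier, to defend selecting the intervention group by desk presence: "Participants will not receive any (noteworthy, see [39]) UVB exposure (that could influence the serum 25(OH)D) unless they are allocated to the intervention group". The same section accepts that knowing one's allocation can influence sleep and fatigue.

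**Control condition.** Section 3 states: "The control group will not be exposed to artificial UVB radiation and will not receive a lamp at their desk".

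**Entry.** Section 4.3 excludes people "Currently taking or planning to take oral vitamin D3 supplements or have been taking D3 supplements during the past 4 weeks", and likewise planned sunbed use or use in the past 4 weeks.

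**Follow-up.** On intake, section 7.1.2 says that "vitamin D related food intake during the past four weeks will be collected", and section 7.4.1.2 adds that "food intake will also be measured in week 4 and 8". The daily diary (sections 7.1.2 and 7.4.1.3) records desk presence, time outside including weekends, and uncovered body parts, in both arms. Section 7.4.1.3 combines time outside with KNMI data to compare natural UVB between groups.

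**Analysis.** Section 7.2 promises control for desk presence, time outside and vitamin D from food. The primary ANCOVA in section 9 names desk presence and time outside.

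**The concern.** A serum level cannot be misreported, but it can be changed. Participants are told that the study concerns artificial UVB and vitamin D levels (section 7.4), and controls know that they have no lamp. A control who responds by starting a supplement or using a sunbed raises the primary endpoint in the arm that is meant to show the untreated decline.

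The protocol itself treats these two sources as able to move 25(OH)D, since it excludes people who use or plan to use them. Section 1 calls the dietary contribution generally too low to maintain sufficient levels. The follow-up described therefore tracks the intake source that the protocol regards as weak, and not the two that it thought strong enough to exclude.

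What is at stake is the reading of the week-8 difference. If it is small, nobody could tell a weak lamp from controls who found vitamin D elsewhere. Section 1 says that the pilot is to inform a larger study, so the ambiguity would carry forward. This is also not a matter that can wait for a statistical analysis plan, because no analysis can use data that were never collected.

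**Working it through.** **1. The plan's own figures (section 4.4).** Expected change to week 8 is -22.3 nmol/L in controls and -13.5 in the intervention group, so the sizing difference is 22.3 - 13.5 = 8.8 nmol/L. With SD 8.4, the standardised difference is 8.8/8.4 = 1.05. At alpha 0.05 and power 0.90, a one-sided two-sample t-test needs 16.33 per group, so 17, which matches the stated figure (a two-sided test needs 20.16, so 21). At the actual 14 per group, power for 8.8 nmol/L is 76% two-sided or 85% one-sided. Sidedness is a separate matter; these values serve here only as a baseline.

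**2. What is recorded for each source of vitamin D.**

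| Source | At entry | During follow-up | Use in analysis |
|---|---|---|---|
| Food | no criterion | baseline, weeks 4 and 8 | promised in 7.2; not named in the primary ANCOVA |
| Supplements | current, past 4 weeks or planned: excluded | none described | none |
| Sunbeds | past 4 weeks or planned: excluded | none described | none |
| Time outside | no criterion | diary, both arms, weekends included | covariate; KNMI-based comparison of groups |
| Exposed skin | no criterion | diary, both arms | dose in an exploratory mixed model |

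The gap is confined to the second and third rows.

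**3. Effect on the arm difference.** If k of 14 controls each end g nmol/L higher than they otherwise would, the control mean rises by k x g/14 and the arm difference falls by the same amount. If k intervention participants do so, the difference rises by k x g/14.

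**4. A value of g from the protocol, for sunbeds.** Section 4.4 reports a rise of 13.9 nmol/L after three sunbed sessions, and 8.8 nmol/L one month later. (This 8.8 equals the sizing difference, but is a separate quantity.)

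- One control: 8.8/14 = 0.63 and 13.9/14 = 0.99 nmol/L. As shares of the sizing difference: 0.63/8.8 = 7% and 0.99/8.8 = 11%.
- Three controls: 3 x 8.8/14 = 1.9 and 3 x 13.9/14 = 3.0 nmol/L, or 21% and 34%.

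**5. A value of g for supplements.** The protocol gives none. Assuming 10 to 30 nmol/L, one control costs 10/14 = 0.7 to 30/14 = 2.1 nmol/L, or 8% to 24% of 8.8.

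**6. Effect on power**, for g = 10 nmol/L, which lies between the two sunbed figures. Two-sided t-test, 14 per group. The last column adds the variance from mixing users and non-users: with p = k/14, control variance is 8.4² + p(1-p)g², averaged with 8.4² for the other arm.

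| k | Remaining difference | Power, SD 8.4 | Power, added variance |
|---|---|---|---|
| 0 | 8.8 | 76% | 76% |
| 1 | 8.09 | 69% | 67% |
| 2 | 7.37 | 61% | 57% |
| 3 | 6.66 | 52% | 48% |

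**The case against.** **Screening already addresses these sources.** Planned use is an exclusion, confirmed by e-mail and checked again by telephone (sections 4.1 and 7.4). Every participant has therefore said that they intend neither. This stands as a reason to expect few users. It does not verify what people do after learning their arm.

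**The questionnaire may already ask.** Its content is in a separate file (section 7.4.1.2) that is not shown, and the participant information is not shown either. This stands: the supportable statement is that the protocol text describes no such item, and the fix is conditional on that.

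**Travel.** A reader might infer that a sunny trip would go unseen. It would not: the diary would show the hours outside and the absence from the desk, and time outside is in the primary model. Only the place is missing, so KNMI data would assign the wrong UV level. Nor do the documents give a reason for travel to differ by arm.

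**Blood results.** A reader might also infer that participants see their values during the trial and react to them. Section 7.3.3 says: "If participants have any questions regarding the gathered blood values, they can turn to their general practitioner or contact DVU". It also says that no diagnosis or advice will be given. It does not say that values are returned, or when, so no argument should rest on this route.

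**The usual direction is conservative.** Use by controls pulls the difference towards zero and would not create a false benefit. That is the more plausible direction, but it is not guaranteed, because use in the intervention arm works the other way.

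**Conclusion.** The statement that 25(OH)D will not be affected by non-blinding is unsupported. The reason given covers UVB exposure and leaves out vitamin D intake. The protocol text describes no follow-up record of supplement or sunbed use, so use that differs by arm would go unrecorded, unless the unseen questionnaire file asks about it.

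The size is modest per person: 0.6 to 1.0 nmol/L for each control, 7% to 11% of the sizing difference. This assumes that the sunbed response quoted in section 4.4 carries over to a control in this trial. It matters because the arms hold 14 and the study is already below its own calculated 17 per group. The number of such controls is unknown.

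A reader might multiply a high supplement gain by several controls and conclude that most of the effect could vanish; three controls at 30 nmol/L would remove 3 x 30/14 = 6.4 of 8.8 nmol/L, or 73%. The documents support neither input. A gain of 30 is 1.7 times the 17.6 nmol/L that the protocol simulates for the lamp under optimal conditions, and every participant has been screened for planned use. That figure should not set the weight of the point.

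**What to change.** 1. In section 7.2, replace the sentence with a statement that non-blinding could affect 25(OH)D through behaviour, that the open design follows from the number of luminaires, and that the relevant behaviour is recorded in both arms.
2. Add two items to the week 4 and week 8 questionnaires in both arms, unless the questionnaire file already holds them: any vitamin D supplement use, with start date, and any sunbed use. An item on stays abroad is optional, because KNMI data do not apply there.
3. Report the answers by arm.
4. Keep all participants in the primary analysis whatever they report. Show a supportive sensitivity analysis of the week-8 difference without reported users, and state that it conditions on behaviour after allocation and can itself introduce bias with 14 per arm.

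The cost is a wording change, two short items (three with the optional one), one extra analysis, and about one more minute per questionnaire. The items rely on self-report, so they reduce the gap and do not close it.
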